#### SF36

SF-36 is a set of generic, coherent, and easily administered quality-of-life measures. These measures rely upon patient self-reporting and are now widely utilized by managed care organizations and by Medicare for routine monitoring and assessment of care outcomes in adult patients.

#### Seattle Angina Pectoris Questionnaire

The SAQ is a self-administered, disease-specific measure for reproducible, and sensitive to clinical change. This instrument was developed and validated by John Spertus, Director of Cardiovascular Education and Outcomes Research at the Mid America Heart Institute and Professor of Medicine at the University of Missouri – Kansas City.

The SAQ quantifies patients’ physical limitations caused by angina, the frequency of and recent changes in their symptoms, their satisfaction with treatment, and the degree to which they perceive their disease to affect their quality of life. Each scale is transformed to a score of 0 to 100, where higher scores indicate better function (e.g. less physical limitation, less angina, and better quality of life).

#### Minnesota Living with Heart Failure Questionnaire

The Minnesota Living with Heart Failure Questionnaire (MLHFQ) is one of the most widely used health-related quality of life questionnaires for patients with heart failure (HF). It provides scores for two dimensions, physical and emotional, and a total score. However, there are some concerns about its factor structure and alternatives have been proposed, some including a third factor representing a social dimension.

### Plans to promote participant retention and complete follow-up {18b}

Upon enrollment and randomization, the investigators will make every reasonable effort to follow the study subject throughout the entire study period. The subject is free to withdraw its written informed consent at any time. The reason for withdrawal should, if available, be documented in the subject’s medical file and in the CRF. When a subject withdraws or is withdrawn from the clinical investigation, a final clinical evaluation should be performed, documented in the medical record and in the CRF.

Participant retention will be increased by schedule strategies, e.g. including the patients in the high-risk cardiac surgery outpatient program follow-up procedure. Participants will also be reminded of the study via telephone calls from the research team.

### Data management {19}

Data entry from paper-based CRF into the statistical software SPSS will be processed by the study team. Validation of data is made by programmed checks of range, validity, and consistency. If necessary, queries are made by the study software or an authorized person. Based on the queries the investigator can check and clarify discrepancies.

After the record of all entries and clarification of all queries, the data base will be closed at the completion of the study. This performance must be documented.

### Confidentiality {27}

All local legal requirements regarding data protection will be adhered to. All study findings and documents will be regarded as confidential. The Investigator and members of the research team must not disclose any information without prior written approval from the Sponsor.

The pseudonymity of patients participating must be maintained. Throughout documentation and evaluation, the patients will be recognized on CRFs and other documents by age and identification number. Documents that identify the patient personally (e.g. the signed informed consent) must be maintained in confidence by the Investigator. The patients will be told that all study findings will be stored on a computer and handled in the strictest confidence.

### Plans for collection, laboratory evaluation and storage of biological specimens for genetic or molecular analysis in this trial/future use {33}

#### Biosamples

At the scheduled visit, blood specimens and urine samples should be collected, whereas fasting is not required. The specimens will be forwarded to the cardiosurgical research laboratory in a pseudonymous manner, which will perform the analysis.

Data arising from clinical genotyping will be subject to the confidentiality standards.

Blood and urine samples will be taken during screening, 4–12h post-surgery, 48–52h post-surgery, day 90 and day 360.

#### Left ventricular biopsies and transcriptomics/epigenomics

Intraoperative left-ventricular biopsies are performed during reperfusion phase 15 min after shock wave therapy. Two samples per treated area are collected using a 14-gauge coaxial needle. For this purpose, a standardized semi-automated biopsy system is used (Semi-Automatic Biopsy System, TSK Lab, The Netherlands) to guarantee reproducibility between patients as described previously (Treibel TA, et al. 2016, Zile MR, et al. 2015). Obtained samples are immediately washed in ice-cold saline (0.9% NaCl) and transferred in liquid nitrogen as described elsewhere (Meder B et al. 2017). Samples are transported on liquid nitrogen to the cardiosurgical laboratory, where isolation of RNA and DNA is performed. RNA and samples are thereafter subjected to screening analysis including deep sequencing, while DNA samples are analysed for high-density epigenome-wide mapping of DNAmethylation (IMGM Laboratories, Munich, Germany). Subsequent bioinformatic processing is performed in cooperation with Priv.-Doz. [name] (Institute of Bioinformatics, MUI).

## Statistical methods

### Statistical methods for primary and secondary outcomes {20a}

#### Efficacy analysis

The primary efficacy variable is the LVEF absolute change from baseline, i.e. the intra-patient difference or change between the pre-treatment (baseline) value day 0 and the value measured at day 360. This variable is quantitative and continuous and will be presented as a mean value with 95% confidence intervals. Change in mean (μ) LVEF from baseline to day 180, defined as delta ΔLVEF, will be analysed using an analysis of covariance (ANCOVA) adjusted for LVEF at baseline (as outlined in Guideline on adjustment for baseline covariates in clinical trials EMA/CHMP/295050/2013, 5.6 ‘change from baseline’ analyses) The main study hypotheses will thus be formulated as:

$$\begin{array}{c}\mathrm H0:\;\mathrm\mu\;\;\mathrm{{\triangle}LVEFcontrol}\;=\;\mathrm\mu\;\;\mathrm{{\triangle}LVEFshockwave}\\\mathrm H1:\;\mathrm\mu\;\;\mathrm{{\triangle}LVEFcontrol}\;\neq\;\mathrm\mu\;\;\mathrm{{\triangle}LVEFshockwave}\end{array}$$

In case of severe deviations from a normal distribution, the change in LVEF from baseline to day 360 will be analysed with the non-parametric Mann-Whitney U test.

Additionally, ANOVA for repeated measurements will be applied in order to analyse LVEF changes across the full study period (day 0, day 180, day360).

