### Outcomes {12}

Primary endpoints:Efficacy: Improvement in LVEF measured by cardiac MRI from baseline to 360 days.Safety: Occurrence of device-related complications (adverse device effects or serious adverse device effects) within 360 days.

Secondary endpoints:Endpoints related to the efficacy are changes in the following parameters within a time frame of 360 days:6-min walk test distanceNYHA functional classSerum nt-proBNP levelsRenal function, measured by glomerular filtration rate (GFR)Seattle Angina Pectoris Questionnaire (SAQ)36-item short-form survey (SF36)Minnesota Living with Heart Failure Questionnaire (MLHFQ)Secondary safety-related endpoints include the following observations within a time frame of 6 days:Occurrence of ventricular arrhythmia during the hospital stayOccurrence of device-related peri-operative myocardial damage detected by a rise of cardiac biomarkers: creatine kinase (CK-MB) and troponin T (TropT)Occurrence of signs of device-related infection detected by a rise of C-reactive protein (CRP) or leukocytosis during the hospital stay

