### Interim analyses {21b}

Two main analyses are planned: (a) An interim analysis when at least 20 participants per group had finished their 360-day follow-up for the primary endpoints, to assess the safety and to allow for an early halt to the recruiting process. (b) A final analysis after 80 patients. For both analyses, the significance level alpha will be set to 0.0294 according to the alpha spending plan proposed by Pocock.

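### The protocol ties its main LVEF test and hypotheses to day 180, although the declared primary endpoint is the change to day 360

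*Protocol article*

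**What the plan says.** The Outcomes {12} section gives the primary efficacy endpoint as "Improvement in LVEF measured by cardiac MRI from baseline to 360 days". The Efficacy analysis section opens consistently with this, describing the primary variable as the "change between the pre-treatment (baseline) value day 0 and the value measured at day 360". The Abstract places the endpoint at 12 months, and Interim analyses {21b} times the interim look "when at least 20 participants per group had finished their 360-day follow-up for the primary endpoints".

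Two sentences after its opening, the Efficacy analysis section states the main analysis for a different quantity, the change in mean "LVEF from baseline to day 180, defined as delta" ΔLVEF, to be tested by an ANCOVA with baseline LVEF as covariate. It continues "The main study hypotheses will thus be formulated as", and H0 and H1 are then written in ΔLVEF. If the data depart severely from normality, "the change in LVEF from baseline to day 360 will be analysed with the non-parametric Mann-Whitney U test". A repeated-measures ANOVA over days 0, 180 and 360 is added as a further analysis.

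The sections on guideline-directed medical therapy confirm that LVEF is measured by MRI at both day 180 and day 360, so either change can be computed.

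**The concern.** The sentence that defines the tested quantity is the one that fixes what the trial sets out to show. Here it gives a different time point from the endpoint it is meant to serve. Three things follow if it is applied as written.

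- The main baseline-adjusted comparison, and with it H0 and H1, concerns 6-month rather than 12-month LVEF.
- Switching from ANCOVA to Mann-Whitney changes the time point as well as the method, so a feature of the observed data decides which endpoint is tested.
- The interim look waits for 360-day completion but would then run an ANCOVA on day-180 values.

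Because both measurements will exist, an analyst could defend either reading from the text. A choice made after results are known could not be told apart from an honest correction.

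**Working it through.** **1. Time point in each place it is stated**

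| Place in the protocol article | Time point |
|---|---|
| Abstract, Methods | 12 months |
| Outcomes {12}, primary efficacy endpoint | day 360 |
| Efficacy analysis, primary variable | day 360 |
| Efficacy analysis, definition of ΔLVEF and ANCOVA | **day 180** |
| Efficacy analysis, H0/H1 (written in ΔLVEF) | **day 180**, by that definition |
| Efficacy analysis, Mann-Whitney fallback | day 360 |
| Efficacy analysis, additional repeated-measures ANOVA | days 0, 180 and 360 |
| Interim analyses {21b} | day 360 |

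No section names day 180 as primary or co-primary, and none specifies an ANCOVA at day 360. The day-180 definition stands alone, but it controls the main test.

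**2. Does the sample size depend on the disputed time point?**

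Inputs from the Conservative method section: mean improvements 10.4 and 4.5, SD 8.7, two-sided alpha 0.05, power 0.80, 10% loss.

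- d = (10.4 − 4.5)/8.7 = 5.9/8.7 = 0.678.
- A two-sample t-test (noncentral t) needs 35.1 per arm, rounded up to 36, so 72 in total. Power at 36 per arm is 0.81.
- Allowing for Mann-Whitney efficiency, 35.1/(3/π) = 36.8, so 37 per arm or 74 in total, within 2 patients of the stated figure.
- 72/0.9 = 80 enrolled.

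The stated 72 and 80 reproduce. The inputs carry no time point, so the correction leaves them unchanged.

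**3. Does the 0.0294 level leave room for a second time point?**

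The critical value is c = Φ⁻¹(1 − 0.0294/2) ≈ 2.178. Two looks at one endpoint, each at this level, give an overall type I error of 0.0500 at half information and 0.0489 at 40/72 = 0.556. The two looks use essentially the whole 5%.

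Suppose, as a condition and not as the plan, that success could be claimed on either time point at a single look. The error is then P(|Z₁| > c or |Z₂| > c), with correlation ρ between the two test statistics. The documents do not give ρ, so a range is assumed:

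| Assumed ρ | Error at one look (nominal 0.0294) |
|---|---|
| 0.5 | 0.054 |
| 0.7 | 0.050 |
| 0.9 | 0.042 |

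**4. Can a power loss be attached to the day-180 reading?**

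No. It would need the treatment difference at day 180, which is not given. The 5.9-point difference has no stated time point either.

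**The case against.** The strongest reply is that this is a one-number slip. Every other statement of the primary time point is day 360 or 12 months, including the opening of the same section and the fallback test. A sensible analyst would run the ANCOVA at day 360. This is probably right, and it limits how hard the point should be pressed. It does not remove the point, because the error sits in the sentence that defines the hypotheses and day 180 is a genuine MRI visit. Nor can it be left to an unseen analysis plan, since the article states the test explicitly and states it inconsistently.

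Four stronger readings are tempting, and the documents do not support them.

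- *The day-360 endpoint has no parametric analysis.* The additional repeated-measures ANOVA is parametric and includes day 360, and the day-360 change is also to be reported as a mean with a 95% confidence interval. What is missing is a baseline-adjusted ANCOVA, or any other named main parametric test, at day 360.
- *The confirmatory test is settled at day 180.* That takes one sentence over all the others. The protocol contradicts itself, and the fallback route does test day 360.
- *Two primary tests are planned without multiplicity control.* No section plans to claim success on either time point. The error rates in the working describe a freedom left open, not a planned procedure.
- *Power falls to a stated figure.* At 36 per arm and level 0.0294, a single-look t-test has power 0.742, 0.643, 0.477 or 0.223 if 100%, 90%, 75% or 50% of the 5.9 points is present at day 180. These fractions are invented scenarios. They ignore the interim look and the baseline adjustment, and a larger day-180 effect is equally undocumented. The fall from 81% to the 74% starting value comes from using 0.0294 instead of 0.05, which is a separate issue.

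**Conclusion.** The contradiction is real and in the current text. As written, the main ANCOVA and H0/H1 concern the change to day 180, while the declared primary endpoint is the change to day 360. The latter is otherwise reached only through the Mann-Whitney fallback and the additional repeated-measures ANOVA, and a distribution check would decide the time point tested. It should be corrected even if it is only a slip, because it leaves the choice of time point open after data are seen.

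Its size is not a power figure. If that freedom were used, the false-positive rate at one look would be about 4.2% to 5.4% instead of 2.94%, under an assumed correlation of 0.9 to 0.5. This is illustrative. The conclusion itself rests on the text alone and needs no numerical assumption.

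**What to change.** In the Efficacy analysis section, define ΔLVEF once as LVEF at day 360 minus LVEF at baseline. Use that definition in the ANCOVA sentence, in H0 and H1, and in the Mann-Whitney fallback, so that a change of method cannot change the time point. Label any day-180 comparison as supportive. Calling it secondary would add an endpoint, since Outcomes {12} lists no LVEF measure among the secondary endpoints.

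Record the change as a dated correction before unblinding. It needs no new data and leaves 72 evaluable and 80 enrolled as they are. The wording change is small, but if it counts as substantial, the section on protocol amendments {25} requires a formal amendment signed by all original signatories, with ethics committees informed and the approvals named there obtained. At the article's status date of 11.11.2022 recruitment had closed, and the last patient's last visit was expected in April 2023, so there was still time to make the correction before the final analysis.

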#### Conservative method

This method is considered the highest standard deviation found in both aforementioned studies. Assuming an effect size (Cohens d) of 0.678 for baseline/follow-up differences between groups (mean improvement; intervention: 10.4 ± 8.7, control 4.5 ± 8.7) on LVEF, 72 participants (36 intervention/36 control) were needed for statistical analysis with an adequate power, assuming an alpha risk of 0.05 (two-sided) and a beta risk of 0.20 (non-normal distributed). With an estimated loss to follow-up (mortality and dropout) of 10%, 80 patients have to be enrolled to ensure that 72 patients can be analysed.

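### The non-normality fallback for the primary LVEF analysis is an unadjusted Mann-Whitney test, which drops the baseline covariate and no longer tests the stated difference in means

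*Protocol article*

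**What the plan says.** Protocol article, Efficacy analysis {20a}:

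- The outcome: "The primary efficacy variable is the LVEF absolute change from baseline", taken from day 0 to day 360 and reported as a mean with a 95% confidence interval.
- The primary test: the change "will be analysed using an analysis of covariance (ANCOVA) adjusted for LVEF at baseline", with a regulatory guideline on baseline covariates cited in support. H0 and H1 are written as equality and inequality of the mean changes.
- The switch: its condition is worded "In case of severe deviations from a normal distribution". When that condition is met, the section replaces the primary test and says that "the change in LVEF from baseline to day 360 will be analysed with the non-parametric Mann-Whitney U test". No covariate is mentioned for this test.

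Conservative method {14}: the sample size rests on unadjusted change scores, "Assuming an effect size (Cohens d) of 0.678 for baseline/follow-up differences between groups" ("intervention: 10.4 ± 8.7, control 4.5 ± 8.7"), and carries the label "a beta risk of 0.20 (non-normal distributed"), so non-normality was considered at planning. Interim analyses {21b} sets alpha to 0.0294 at each of two analyses. Who will be blinded {17a} says that data analysts are blinded to group assignment.

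The same Efficacy analysis paragraph writes the ANCOVA for another visit ("Change in mean (μ) LVEF from baseline to day 180, defined as delta ΔLVEF"). That conflict must be reconciled, but it is a separate matter. Below I take day 360 as the time point of both tests.

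**The concern.** Non-normality is a reason to change how inference is done. It is not a reason to stop adjusting for baseline. Mann-Whitney on change scores uses baseline LVEF only by subtraction, which fixes its coefficient at 1, whereas ANCOVA estimates the coefficient. Any patient with a change score has a baseline value, so adjustment loses no one.

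The switch also changes the question. The hypotheses and the planned presentation concern means. Mann-Whitney compares distributions by rank and gives no estimate of the mean difference. The confirmatory method then depends on how the outcome data look.

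At stake is power at alpha 0.0294 in a trial with about 72 analysable patients, and a primary result whose meaning depends on which branch was taken.

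**Working it through.** **1. The plan's own figure.** d = (10.4 − 4.5)/8.7 = 5.9/8.7 = 0.678. A two-sample t test (noncentral t, two-sided alpha 0.05) needs 36 per arm, with power 81.0%. This reproduces the stated 72, and 72/0.90 = 80 enrolled. For Mann-Whitney with normal data (efficiency 3/π relative to the t test) the figure is 37 per arm.

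**2. What the covariate is worth with normal data.** Assume equal SDs σ at both visits and correlation ρ (not in the documents). The variance of change is 2σ²(1 − ρ). The residual variance after adjustment is σ²(1 − ρ²). Their ratio is (1 + ρ)/2, so the ANCOVA effect size is 0.678/√((1 + ρ)/2): 0.783, 0.758 and 0.736 at ρ = 0.5, 0.6 and 0.7. With 36 per arm and alpha 0.0294:

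| ρ | ANCOVA | Mann-Whitney on change | Difference (points) |
|---|---|---|---|
| 0.5 | 86.1% | 72.0% | 14.1 |
| 0.6 | 83.7% | 72.0% | 11.7 |
| 0.7 | 81.3% | 72.0% | 9.3 |

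Over ρ from 0.3 to 0.9 the difference runs from 18.8 down to 4.5 points.

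**3. Power where the switch would be triggered.** Step 2 describes data for which the plan would not switch, so I simulated other error shapes. Setup: 36 per arm, baseline normal with SD 8.7/√(2(1 − ρ)), day-360 LVEF = ρ × baseline + error + 5.9 × treatment, error SD scaled so that the SD of change is 8.7, alpha 0.0294, 10,000 runs per row (Monte Carlo error at most 0.5 point). The adjusted rank test is Mann-Whitney applied to residuals from regressing change on baseline. Power in % at ρ = 0.5 / 0.7:

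| Error shape | ANCOVA | Mann-Whitney on change | Rank test on adjusted residuals | Rank-transform ANCOVA |
|---|---|---|---|---|
| Normal | 85.9 / 81.0 | 71.5 / 71.9 | 83.7 / 79.0 | 83.1 / 76.6 |
| t, 3 df | 87.9 / 83.9 | 86.6 / 89.5 | 97.6 / 96.2 | 96.1 / 90.4 |
| Exponential | 84.8 / 80.0 | 84.2 / 87.9 | 97.3 / 95.8 | 94.3 / 86.1 |
| Lognormal | 86.1 / 84.0 | 94.8 / 97.8 | 99.9 / 99.8 | 99.5 / 96.8 |
| 10% outliers (5 × SD) | 84.3 / 80.3 | 90.1 / 93.9 | 99.3 / 98.5 | 98.2 / 92.8 |
| Uniform | 85.6 / 79.9 | 67.7 / 66.5 | 79.5 / 73.6 | 78.7 / 72.1 |

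Differences from Mann-Whitney on change:

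- **Adjusted-residual rank test:** better in every row, from 99.8 − 97.8 = 2.0 (lognormal, 0.7) to 97.3 − 84.2 = 13.1 points (exponential, 0.5).
- **Rank-transform ANCOVA:** usually better, but 1.0 to 1.8 points worse under exponential, lognormal and outlier errors at ρ = 0.7.
- **Ordinary ANCOVA:** better by 14.4 / 9.1 points (normal) and 17.9 / 13.4 (uniform), about level under t and exponential errors at ρ = 0.5, and up to 13.8 points worse under lognormal errors.

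**4. Type I error.** With no treatment effect and the same error shapes, each test used alone rejected in 2.1% to 3.3% of runs at nominal 2.94%. Taking the smaller of the ANCOVA and Mann-Whitney p-values rejected in 4.1% to 4.8%. A fixed normality rule (Shapiro-Wilk on residuals, my assumption) gave 4.7% to 5.5% at nominal 5%.

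**The case against.** The best defence has four parts.

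- **The fallback is named in advance and suits its trigger.** Under skew, heavy tails or outliers, Mann-Whitney matches or beats ordinary ANCOVA. A reader might infer from step 2 that the switch costs 9 to 14 points whenever it is used. The documents do not support that: those figures assume near-normal data and a correlation the protocol does not give. This part stands, but it compares a rank test with a mean-based test. Against a baseline-adjusted rank test, the named fallback loses under every error shape tried.
- **Discretion is limited.** A reader might infer that the primary test can be picked after seeing the results. Section {17a} blinds the analysts, one alternative is named, and a fixed rule keeps type I error near nominal. The rise to about 0.04 to 0.05 needs free choice of the smaller p-value, which nothing in the text suggests. The threshold for a severe deviation may be in an analysis plan that is not shown, so its absence is not counted here.
- **The sample size never relied on the covariate.** This stands. It was built on unadjusted change scores, and at the planning alpha of 0.05 Mann-Whitney with normal data still has 79.1% power with 36 per arm. The point does not show that the trial is underpowered.
- **Adjusted rank tests do not test a difference in means either.** This is correct, and is why they belong in a sensitivity analysis. A permutation test of the ANCOVA treatment statistic keeps the mean difference as its target.

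**Conclusion.** The point holds as a poor choice of method stated in the protocol itself. The replacement test gives up the baseline covariate without need and changes the hypothesis. Dropping the covariate costs about 2 to 13 points of power against a rank test on baseline-adjusted residuals, including under the skewed and heavy-tailed errors that would trigger the switch. This rests on an assumed correlation of 0.5 to 0.7, 36 per arm, alpha 0.0294, the protocol's difference of 5.9 with SD 8.7, a normal baseline and a constant treatment shift. No general loss against ordinary ANCOVA and no type I error inflation under a fixed rule can be claimed. The matter deserves correction but does not threaten the trial's validity.

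**What to change.** 1. Name baseline-adjusted ANCOVA of LVEF at day 360 as the single primary test, and delete the conditional switch. Reconcile the day-180 wording separately.
2. Pre-specify one baseline-adjusted robust sensitivity analysis: a permutation test of the ANCOVA treatment statistic, or a rank test on baseline-adjusted residuals. Simple rank-transform ANCOVA is a weaker choice.
3. If a non-normal fallback is kept, make it baseline-adjusted, state its criterion, and apply the same rule at the interim and final analyses.

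The cost is wording, with the same data and no new measurements. The article's status entry has recruitment closed and last follow-up pending, so at that date the change could still be made and dated before database lock, by people without access to results by arm.

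There is a downside. With severely skewed or heavy-tailed data, ANCOVA as sole primary test can have less power than a rank test (84.0% against 97.8% for even the unadjusted Mann-Whitney in the lognormal case at ρ = 0.7). The adjusted sensitivity analysis would show this but would not replace the primary result.

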### Methods for additional analyses (e.g. subgroup analyses) {20b}

No subgroup analyses have been planned for this trial. To investigate the robustness of the primary endpoint analysis performed in the intention-to-treat (ITT) population and to examine the possible effects of missing data, sensitivity analyses are planned. These analyses will be performed in the ITT population without the imputation of missing values, in a population with complete data sets only, and in an ITT population where the LVEF of deceased patients is set to 0%.

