#### Intention-to-treat population

The intention-to-treat population will consist of all patients who were enrolled to the study and who have given their informed consent. In case of withdrawals and missing data, the Last observation carried forward (LOCF) procedure will be applied where appropriate. The ITT population serves as the primary analysis population.

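### The supplementary repeated-measures ANOVA of LVEF counts pre-treatment day 0 as an outcome level: its arm main effect is diluted and its arm-by-time test does not isolate day 360

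*Protocol article*

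**What the plan says.** The Efficacy analysis section defines the primary variable as the "change between the pre-treatment (baseline) value day 0 and the value measured at day 360". LVEF change "will be analysed using an analysis of covariance (ANCOVA) adjusted for LVEF at baseline", and the null and alternative hypotheses follow from that model. The section then adds a longitudinal analysis: "ANOVA for repeated measurements will be applied in order to analyse LVEF changes across the full study period (day 0, day 180, day360"). The pre-treatment value is thus one of three outcome levels. No other longitudinal LVEF model is named.

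Three other sections bear on the point:
- Intention-to-treat population: "In case of withdrawals and missing data, the Last observation carried forward (LOCF) procedure will be applied where appropriate", and "The ITT population serves as the primary analysis population".
- Methods for additional analyses {20b}: "These analyses will be performed in the ITT population without the imputation of missing values, in a population with complete data sets only", plus a run with LVEF of deceased patients set to 0%.
- Interim analyses {21b}: alpha is 0.0294 at both the interim and the final analysis.

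Under Concealment mechanism {16b}, the allocation envelope is opened during surgery once the bypasses are established. Baseline LVEF is therefore measured before allocation.

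**The concern.** Randomisation makes the expected arm difference at day 0 zero. The ANCOVA uses that value properly, as a covariate. The repeated-measures ANOVA treats it as a response, and its two tests involving arm then answer different questions:

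- The arm main effect compares the average of three visits, one of which cannot carry a treatment effect.
- The arm-by-time interaction asks whether the arm difference varies over the three visits. It names neither the visit nor the direction.

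Neither is the arm difference at day 360, which is the primary variable. Because no other named analysis combines the day-180 and day-360 scans, readers are likely to set this one beside the primary result. A non-significant outcome could then be taken as evidence against a positive ANCOVA when it only reflects the form of the test.

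**Working it through.** **Inputs from the protocol.** Conservative method: "mean improvement; intervention: 10.4 ± 8.7, control 4.5 ± 8.7) on LVEF, 72 participants (36 intervention/36 control) were needed". The difference is 10.4 − 4.5 = 5.9, the SD of change 8.7, n = 36 per arm. Alpha is 0.0294 (Interim analyses).

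**Inputs assumed, because the protocol does not give them.** Equal correlation ρ between any two visits (compound symmetry), 0.5 to 0.7. The day-180 effect is either full (5.9) or half (2.95). The ANCOVA used for comparison is at day 360.

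**The plan's own figure.** d = 5.9/8.7 = 0.678. A two-sided t-test at 0.05 has power 0.799 with 35 per arm and 0.810 with 36, so 36 per arm = 72 is reproduced; 72/0.9 = 80.

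**SD per visit.** σ = 8.7/√(2(1−ρ)): 8.70 at ρ = 0.5 and 11.23 at ρ = 0.7.

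**Day-360 ANCOVA.** SE = σ√(1−ρ²)·√(2/36).
- ρ = 0.5: SE 1.776, ratio 5.9/1.776 = 3.32, power 0.86.
- ρ = 0.7: SE 1.891, ratio 3.12, power 0.81.

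**Arm main effect.** It estimates the mean arm difference over the three visits:
- full: (0 + 5.9 + 5.9)/3 = 3.93, which is 67% of 5.9;
- half: (0 + 2.95 + 5.9)/3 = 2.95, which is 50%.

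SE = σ√((1+2ρ)/3)·√(2/36): 1.674 at ρ = 0.5 and 2.368 at ρ = 0.7.

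**Arm-by-time interaction.** Noncentrality λ = (36/2)·Σ(δⱼ − δ̄)²/(σ²(1−ρ)), with 2 and 140 df. Since σ²(1−ρ) = 8.7²/2 = 37.845, λ does not depend on ρ.
- full: Σ = 23.21, λ = 18 × 23.21/37.845 = 11.04, power 0.79.
- half: Σ = 17.41, λ = 8.28, power 0.64 to 0.65 (0.645).

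The zero at day 0 is the reference for this test, so it is not attenuated. Its loss against ANCOVA comes from the 2 df, the missing baseline adjustment and the lack of a day-360 target.

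| Test (alpha 0.0294) | ρ = 0.5 | ρ = 0.7 |
|---|---|---|
| ANCOVA, day 360 | 0.86 | 0.81 |
| Main effect, full day-180 effect | 0.55 | 0.29 |
| Main effect, half | 0.33 | 0.17 |
| Interaction, full | 0.79 | 0.79 |
| Interaction, half | 0.65 | 0.65 |

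**How often the results diverge.** Simulation with complete data on 72 patients, 3,000 trials per setting, same ranges: ANCOVA is significant and the main effect is not in 33–67% of trials. ANCOVA and interaction disagree in either direction in 17–25%; in 10–23% ANCOVA is positive and the interaction is not.

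**Missing scans.** With LOCF, all 80 patients stay in both analyses. Assuming 10% of day-360 and 5–10% of day-180 scans missing at random, the divergence remains: 35–65% for the main effect, 14–23% for the interaction. Without LOCF, a classical repeated-measures ANOVA needs all three scans, and the loss depends on the pattern:
- Loss that is permanent once it occurs: everyone with a day-360 scan also has day 180, so no one is lost beyond those already missing from the ANCOVA (72 kept).
- Independent gaps of 5–10% at day 180: 80 × 0.9 × 0.95 = 68.4 down to 80 × 0.9 × 0.9 = 64.8 kept, against 72 for the ANCOVA.

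**The case against.** The strongest case for the plan is that the analysis is explicitly additional. The hypotheses belong to the ANCOVA, no decision rule uses the repeated-measures result, and two different tests sometimes disagreeing is not an error. The stated aim is change over the study period, which is naturally the interaction, and the protocol nowhere says it will interpret the main effect. An article may also leave the choice of term and contrasts to the analysis plan. All of that limits the weight of the point. It does not remove it, because the article itself fixes the method and its three outcome levels, and the interaction still does not deliver the day-360 difference.

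Two stronger readings are tempting, and the document does not support them:
- A reader might infer that day 0 dilutes both arm tests. It dilutes only the main effect. With a full day-180 effect the interaction has 79% power against 81–86%, a modest loss; the clear loss (65%) needs the assumed half effect.
- A reader might infer that every patient missing a follow-up MRI drops out. LOCF is planned, where appropriate, in the primary ITT population and would keep them. Listwise loss concerns only runs without LOCF. The protocol's single 10% figure for mortality and dropout does not give the pattern by visit, so no firm number can be attached.

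**Conclusion.** The point holds as a recommended improvement to a supplementary analysis. The one named analysis that combines both follow-up MRIs uses a pre-allocation value as a response. Its main effect recovers 67% of the planned effect, or 50% if day 180 shows half of it; its interaction is a 2-df test without a day-360 estimate. It can therefore fail to support a positive ANCOVA although the effect is real.

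The 3.93 and 2.95 follow by arithmetic from the planned difference and the assumed day-180 effect. The powers also rest on compound symmetry and, for ANCOVA and the main effect, on ρ of 0.5 to 0.7. It would go too far to say that the trial's primary conclusion is at risk: that rests on the ANCOVA.

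**What to change.** First reconcile a separate conflict in the same section: the primary variable is defined at day 360, while the ANCOVA sentence names day 180. That settles which ANCOVA the longitudinal model supports.

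Then replace the repeated-measures ANOVA sentence with a mixed model for repeated measures:
- outcomes: LVEF at day 180 and day 360;
- fixed terms: arm, visit, arm-by-visit, baseline LVEF and baseline-by-visit;
- unstructured within-patient covariance;
- all randomised patients with a baseline and at least one follow-up MRI, without LOCF.

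Report the arm difference with its confidence interval at each visit, and name day 360 as the supportive estimate for the primary endpoint. If day 0 is to remain an outcome, an equivalent option is a longitudinal model that constrains the arm means to be equal at day 0.

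The cost is one sentence and a standard procedure, with no new data or patients. The downside is a slightly more complex model that relies on follow-up scans being missing at random; the planned run with LVEF of deceased patients set to 0% can stay beside it.
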